##### Dashboard

The dashboard is the homepage after login and aims to provide a quick overview about the most important components of the program. Users see automated messages from their e-coach (see below), study-related information, module progress, and the last 2 weeks of their drinking diary. They can also plan some activities unrelated to alcohol use and upload a photo reminding them of this activity.

##### E-coach

The e-coach is, on one hand, a real person who can be contacted by e-mail and provide individual guidance. On the other hand, it is also an automated agent that sends e-mails and provides suggestions on the dashboard (e.g., to work through a module or to fill out an assessment if the time has come). One of the purposes of the e-coach is to help reduce attrition.

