## Methods

### Study design

The minimal-guidance Web-based self-help *“Selge” program* will be evaluated within a two-arm non-blinded randomized clinical trial (RCT). Eligible individuals will be randomized to either the online program or the control group (described below). Assessments will occur before randomization (T0; baseline), at 8 weeks (T1; treatment end), and at 6 months (T2; 4-month post-treatment follow-up). We have chosen these three measurement dates to distinguish intervention effects from possible follow-up effects. The control condition website will be accessible to both study conditions, and the actual use of treatment from usual resources assessed at T1 and T2. Participants will be made aware to which treatment arm they have been assigned after their baseline measurement. Participants allocated to the control condition will be provided with access to the full online program after they complete their final follow-up assessment.

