### Randomization and trial flow

The baseline assessment starts with a suicidality screener [13]. Users indicating a higher risk of suicidality are excluded from the study and program and provided with a list of help lines. Users who do not meet the requirements for AUDIT are excluded from the study, but remain free to use the program, nevertheless. Users who fulfill the requirements after the baseline assessment are considered study participants and randomly assigned by a simple server randomization in a 1:1 ratio to either the *“Selge” program* or the control condition (see Fig. 2), informed about their assignment, and given further instructions. Participants in the control group are informed that they can use the program after 6 months, and provided with a help page — “Where to turn” — which is described in detail later in this paper. After 8 weeks (end of treatment), both groups undergo an assessment, as well as 6 months after baseline. An email prompt is sent automatically for each assessment, followed by two additional reminders sent to those who still have not completed the assessment. The last reminder sends a system email to the non-blinded study coordinator who then tries to contact the participant by phone up to twice. Participants are not compensated for completing the follow-up assessments. However, from all participants who complete all assessments, ten will be randomly selected to win a smartphone.

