##### Control condition

Individuals assigned to the control condition are told that they will have access to the complete program in 6 months. In the interim, they only have access to a help page called “Where to turn”, which lists treatment centers (including contact details), psychiatric care providers and further health services. Moreover, they are advised to visit the website www.alkoinfo.ee [16], where they can learn about the principles of alcohol abuse treatment, complete a self-administered test based on the AUDIT [6] (see Fig. 4), and receive personalized feedback.

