### Sample size calculation

A recent meta-analysis [24] showed that combining CBT and MI resulted in statistically-significant reductions in alcohol use, with effect sizes in the small range for internet interventions (*g* = .20). As we aim to compare the *“Selge” program* with a control condition which provides extensive resources and a self-administered test of alcohol abuse, we expect larger effects. The study that comes closest to our design compared online Personalized Normative Feedback (PNF) plus an intensive, but unguided CBT (56 daily sessions plus six weekly follow up sessions) program versus PNF with an online booklet; it also recruited alcohol misusers from the general population and it generated a Cohens’ *d* = 0.20 [11]. As we are offering a minimal-guidance intervention and comparing it to a self-administered test with routine advice on usual treatment, we expect a Cohens’ *d* = 0.23 for the current study. Using G*Power, the sample size required to detect this small effect with 80% power and α = 0.05 is *N* = 596 total (298 per group).

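### Formal follow-up is the same in both arms, but the intervention arm gets at least one extra assessment prompt and an unblinded coordinator makes the calls, so non-response may become arm-dependent

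*Protocol article*

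**What the plan says.** **Common follow-up.** Protocol article, Randomization and trial flow: both groups are assessed at 8 weeks and at 6 months. Each assessment has an automatic e-mail and two reminders to those who have not answered. The last reminder also triggers a system message to the "non-blinded study coordinator who then tries to contact the participant by phone up to twice". No step is restricted to one arm.

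**Intervention arm.** Under Treatment condition, the treatment website is said to include a dashboard. The E-coach section describes an automated agent that sends e-mails and puts suggestions on that dashboard, for example "to work through a module or to fill out an assessment if the time has come". It adds: "One of the purposes of the e-coach is to help reduce attrition".

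**Control arm.** Control condition: "In the interim, they only have access to a help page", with advice to visit a public website. No dashboard or e-coach is mentioned.

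**Expected response and analysis.** The Discussion expects 40–60% follow-up at 6 months and gives no rates by arm. The Data analysis plan specifies multiple imputation, cross-checked with complete cases.

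**The concern.** Prompting for the outcome should not depend on the arm. Here one arm sees a further request to complete the assessment, from a component meant in part to reduce attrition, and the person who telephones non-responders knows the allocation. If either changes who answers, the responders in the two arms are selected to different degrees and the completer comparison carries that difference.

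This matters because about half the primary outcome data are expected to be missing and the planned effect is small ("we expect a Cohens’ *d* = 0.23 for the current study"). Multiple imputation deals with non-response that depends on arm and on observed data. It does not deal with non-response that still depends on the unobserved 6-month AUDIT score once those are taken into account.

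**Working it through.** **1. The plan's own figure.** Two-sample t-test, d = 0.23, two-sided α = 0.05, power 80%: n = 297.7, so 298 per arm and 596 in total. This matches the Sample size calculation exactly (power at 298 per arm is 80.0%). Nothing in this point changes that number.

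**2. Assessment prompts by arm, read from the text.**

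| Prompt | Intervention | Control |
|---|---|---|
| Automatic e-mail | yes | yes |
| Two reminders | yes | yes |
| Up to two calls, unblinded coordinator | yes | yes |
| Dashboard suggestion to complete the assessment | yes | none described |
| E-coach e-mail about the assessment | possibly; not said whether it is separate from the automatic e-mail | none described |

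The clear difference is the dashboard row. The last row is open.

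**3. Illustration of bias.** The documents give neither arm-specific response nor a response–outcome correlation, so both are assumed. Let responders be the top share f of a normal latent variable that correlates ρ with the outcome. The responder mean is then shifted by ρ × φ(z)/f, where z cuts off the share f.

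- f = 0.55: φ(z) = 0.396, and 0.396/0.55 = 0.720.
- f = 0.45: φ(z) = 0.396, and 0.396/0.45 = 0.880.
- Difference between arms: 0.160 × ρ.

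| ρ | Shift (SD) | Share of 0.23 |
|---|---|---|
| 0.1 | 0.016 | 7% |
| 0.2 | 0.032 | 14% |
| 0.3 | 0.048 | 21% |

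**4. Check by a second route.** Bias = (difference in missing share) × (gap between completers and non-completers, in SD, assumed equal in both arms). With 0.55 − 0.45 = 0.10 and an assumed gap of 0.1–0.5 SD, the shift is 0.01–0.05 SD. In either model it is zero if response is equal in the two arms.

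**5. Power is not the issue.** With 298 randomised per arm, observed-case power is 50.8% at 50%/50% response (149 v 149) and 50.4% at 55%/45% (164 v 134). Imbalance as such costs almost nothing; the possible harm is bias.

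**The case against.** The case against is substantial, and much of it stands.

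- **A reader might infer that controls are not chased.** They are: they get the same e-mail, reminders and calls. That only the intervention arm gets e-coach prompts is itself an inference from where the sections sit. The inference is strong for the dashboard. For e-mails it is open, because these may be the common automatic e-mails under the e-coach's name.
- **A reader might infer that follow-up calls are made unequally.** The text does not show this. Calls are triggered by the system and capped at two in both arms. An unblinded caller has the opportunity for unequal effort, no more. The outcomes are self-reported online, so the coordinator does not rate them.
- **The prompt may have faded by 6 months.** The programme lasts 8 weeks, and the article does not say whether e-coach messages continue until the primary endpoint. Attrition in the E-coach section may also mean programme dropout and not only missing assessments.
- **Controls have an incentive of their own.** Study design gives them the full programme after their final assessment. The net imbalance could be nil or reversed.
- **A reader might take 40% and 60% as the two arms' rates.** That gives 0.032–0.097 SD for ρ = 0.1–0.3. The arithmetic is right, but the range expresses uncertainty about overall follow-up, and nothing supports a 20-point gap between arms. The 55% v 45% split is assumed too, and serves only to show scale.
- **The analysis plan already covers part of this.** Imputation handles non-response explained by arm and observed data, and extra prompting alone does not make data missing not at random.

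What survives is narrower: as written, one arm has an additional assessment prompt, allocation is visible to the caller, and neither is needed.

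**Conclusion.** The point holds as a cheap improvement. It is not an error that invalidates the design. The text supports at least one extra assessment prompt in the intervention arm, possibly more, and calls made with knowledge of allocation. It does not establish that response will differ, by how much, or in which direction.

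Under an assumed 10-point difference in response and ρ of 0.1–0.3, the completer contrast would move by 0.02–0.05 SD, or 7–21% of the planned 0.23. The conclusion rests on two readings: that the dashboard is confined to the intervention arm, as the Treatment condition and Control condition sections indicate, and that its assessment prompts are still active when assessments fall due, which the article leaves open for the 6-month visit.

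**What to change.** 1. Send every 8-week and 6-month assessment prompt from one arm-neutral system, with the same content, number and timing in both arms. Limit e-coach and dashboard messages to programme content, or send controls equivalent prompts by e-mail. If the e-coach's assessment e-mails are the common automatic e-mails, say so.
2. Hide the allocation on the coordinator's call list and use one call script.
3. Report 6-month response and the number of contact attempts by arm.

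The cost is message configuration and access rights on the existing platform, with no extra staff and no change to N = 596. If prompts are removed from the intervention arm and not extended to controls, that arm may return slightly fewer responses. The change will not guarantee equal response, since programme engagement and delayed access still differ by design; it removes only the part that comes from unequal prompting.

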##### Social presence

Apart from the e-coach, a strong element of social presence is created via a brief introduction video at the start of each module. The actor seen in those videos is the same as the one depicted on the dashboard as the e-coach representing the *“Selge”* program team. Research suggests that such social factors may improve accountability [14], especially for self-guided programmes. Another social element is six fictional companions, one of whom each participant can select at the start of the program; someone they feel they might identify with, in terms of gender, age, occupation, and/or family background. These companions provide advice and examples at specific points during the modules.

##### Consumption diary

Participants in the intervention group will be asked to track their weekly alcohol use and goals measured in standard drinks throughout the program. Daily goals and actual intake will be displayed on a progression graph with two separate lines, making any deviation of intake from their target evident. A separate online drinking calculator [15] helps users to estimate the number of standard drinks they have consumed, by showing country-specific drinking containers/glasses/bottles, their different volumes in milliliters (ml), alcohol percentages and calories. Next to the calculator results, participants are reminded of their country-specific safe-drinking limits.

##### Control condition

Individuals assigned to the control condition are told that they will have access to the complete program in 6 months. In the interim, they only have access to a help page called “Where to turn”, which lists treatment centers (including contact details), psychiatric care providers and further health services. Moreover, they are advised to visit the website www.alkoinfo.ee [16], where they can learn about the principles of alcohol abuse treatment, complete a self-administered test based on the AUDIT [6] (see Fig. 4), and receive personalized feedback.

**Fig. 4 Fig4:**
[figure not shown]
Self test for alcohol abuse (AUDIT) on alkoinfo.ee (translated from Estonian to English for publication purposes only)

##### Technical specifications

The program website [17] is based on the content management system Drupal 7 and has a responsive design, making it suitable for both desktop computers and mobile devices. All connections from participants and administrators will run SSL-encrypted and password-protected. At any time, any participant will have access to his or her own data only. There are three administrative roles in place: (1) E-coaches have access to some of the participants’ data, like the diary or texts that participants enter during exercises in some modules; this information can assist their coaching activities. (2) Researchers have access to all data from questionnaires and the diary. (3) The administrator has full access to all data, including some technical meta data. All data that participants enter will undergo some input validation, ensuring a certain degree of data quality.

All data will be stored on webservers hosted by TAI at a research institution fileserver catalogue that is accessible to only a limited number of research project members. Data will be exported via Drupal and stored at the principal investigator’s institution on local computers for further processing and local fileservers for archiving. After the study ends, data sets will be stripped of all email addresses and phone numbers. The investigator affirms and upholds the principle of every participant’s right to privacy and ensures that all personnel involved in the study will comply with applicable privacy laws. No subject-identifying data will ever be published or presented at conferences.

#### Measures

Table 2 provides a schedule for each assessment measure. Demographic information will include age, gender, nationality, type of settlement (which major city or rural settlement), educational level, and the type of social engagement (employer, employed, student, retired, unemployed). All self-report questionnaires will be administered online.

**Table 2 Tab2:** Schedule of Assessment Measures

Self-Report Measures	Baseline (T0)	8 weeks (T1)	6 months (T2)
1. Demographics	x		
2. Suicidality Screener (P4)	x		
3. Alcohol Use Disorder Identification Test (AUDIT, main outcome)	x	x	x
4. Self-reported number of standard drinks on typical week over the past 6 months	x	x	x
5. Self-reported number of alcohol-free days on a typical week over the past 6 months	x	x	x
6. Drinking Motives Questionnaire (DMQ-R-5)	x	x	x
7. Motivation for Change	x	x	x
8. Mental Health Inventory (MHI-5)	x	x	x
9. Drug Use (NIDA ASSIST)	x	x	x
10. Customer satisfaction (iCSQ-8)		x	
11. Usage of other resources for intervention or treatment of alcohol use disorders		x	x

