##### Secondary outcomes

Secondary outcomes include:
The self-reported number of (Estonian) standard drinks and alcohol-free days on a typical week over the past 6 months. This measure has been selected for use to allow for comparisons with results from an ongoing study being spear-headed by the World Health Organization [18].Drinking motives are being measured using the Drinking Motives Questionnaire (DMQ-R-5). The DMQ-R measures how people score on four motivational dimensions. Originally developed by Cooper [19], the underlying factor structure was confirmed by Kuntsche et al. [20] in Switzerland. The four motive types are social (e.g., drinking to be sociable, to celebrate, at parties); coping (e.g., drinking because it makes you forget about problems); enhancement (e.g., drinking to feel better or to be able to do things otherwise impossible); and social pressure and conformity (e.g., drinking because others do, to fit in).Motivation for Change (3 items). Participants rate how *important*, how *confident* and how *ready* they are to change their alcohol use, on scales from 0 to 10.Mental health is being measured with the 5-item version of the Mental Health Inventory [21]. The MHI-5 is about recent mental distress and a self-reported diagnosis of depression. It is well validated and easy to use.Treatment retention is defined as the percentage of data fields filled out in the weekly alcohol consumption diary over the 8 weeks of the intervention.Further illicit drug consumption is being accounted for via the NIDA-Modified ASSIST questionnaire [22].The “Customer Satisfaction Questionnaire” for internet interventions (iCSQ-8 [23]) is being used to assess satisfaction with the program in the intervention group. The iCSQ-8 has been extensively studied and results in scores from 8 to 32 (higher = better). We will implement a slightly-adapted version to account for Estonian practices.To check if participants used the resources provided by the program (treatment group only) and/or if they used additional resources (both groups) to treat themselves for their alcohol use, they are asked how many hours they invested in such material. Moreover, they are asked whether they employed professional help (consultation) to reduce their alcohol use (GP, psychologist, psychiatrist, other health specialist); and, if so, how many hours.

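### The 8-week assessment asks about drinks and alcohol-free days over the past six months, so about 69% of its recall window precedes randomisation and the T1 contrast on these two secondary items is probably diluted by an unknown amount

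*Protocol article*

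**What the plan says.** Table 2 (Measures) lists "Self-reported number of standard drinks on typical week over the past 6 months" and "Self-reported number of alcohol-free days on a typical week over the past 6 months", and marks both at T0, T1 and T2. The Secondary outcomes section repeats the window ("standard drinks and alcohol-free days on a typical week over the past 6 months") and gives no shorter one for T1. Its reason for the measure is comparability with a WHO-led study: "This measure has been selected for use to allow for comparisons with results from an ongoing study".

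The Study design section fixes the time origin ("Assessments will occur before randomization (T0; baseline") and places the later assessments "at 8 weeks (T1; treatment end), and at 6 months (T2; 4-month post-treatment follow-up". It then explains the schedule: "We have chosen these three measurement dates to distinguish intervention effects from possible follow-up effects". The Discussion repeats this purpose and accepts that an extra assessment may lower response.

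**The concern.** The look-back is more than three times as long as the time since randomisation at T1. An answer given at 8 weeks therefore describes, for the most part, drinking before anyone was allocated, and it overlaps heavily with what the same person reported at baseline.

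Two readings of the results are at stake. A small or null T1 difference in drinks or alcohol-free days could be taken as a lack of effect at the end of treatment, when the item gave the effect little room to appear. A larger difference at T2 could be taken as a delayed or growing effect, when only the window had moved. The second reading is the one the T1/T2 pair was meant to settle.

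No other scheduled measure fills the gap. The consumption diary is kept by the intervention group only, so it gives no between-arm comparison of drinking during treatment.

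**Working it through.** **The plan's own figure, for reference.** Sample size calculation: d = 0.23, 80% power, α = 0.05 (two-sided according to the Data analysis plan), 1:1 allocation. The normal approximation is n per arm = 2(1.960 + 0.842)²/0.23² ≈ 297. The t-test version gives 297.7, so 298 per arm and 596 in total. This matches the plan. The document gives no figure for the recall window.

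**Windows, in weeks from randomisation (6 months ≈ 26 weeks).**

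| Assessment | Window covered | Before randomisation | Weeks 0–8 (treatment) | After week 8 |
|---|---|---|---|---|
| T0 | −26 to 0 | 26 | 0 | 0 |
| T1 (week 8) | −18 to 8 | 18 | 8 | 0 |
| T2 (week 26) | 0 to 26 | 0 | 8 | 18 |

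- Share of the T1 window before randomisation: (26 − 8)/26 = 69.2%. Share after it: 8/26 = 30.8%.
- Sensitivity: counting 6 months as 24 weeks gives (24 − 8)/24 = 66.7%. If T1 is completed one or two weeks late, the share is 17/26 = 65.4% or 16/26 = 61.5%.
- Overlap: T0 and T1 share 18 weeks, T1 and T2 share the 8 treatment weeks, and T0 and T2 share essentially none.

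**Illustrative dilution.** Visible effect = d × (share of the answer that reflects time since randomisation). The documents state no expected effect for these two items, so the planning value 0.23 is borrowed. It is assumed to act in full from day 1 with an unchanged SD.

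| How respondents answer at T1 | Visible share | Visible effect |
|---|---|---|
| Report the commonest week, mostly before randomisation | near 0% | near 0 |
| Average over the whole window | 8/26 = 31% | 0.23 × 0.308 = 0.071 |
| Report recent weeks only | 100% | 0.23 |

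Under averaging only:

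- With 298 per arm, power is about 14% instead of 80%.
- At the 50–70% T1 follow-up expected in the Discussion (150–210 per arm out of 600), power is about 9–11% instead of 51–65%.
- Detecting 0.071 with 80% power would need about 6,270 participants.

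**Apparent growth.** If the true difference is a constant 0.23 SD from randomisation to month 6, averaging gives about 0.07 at T1 and 0.23 at T2. The ratio is 26/8 = 3.25, and the window alone produces it.

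**The case against.** The best defence is that the window was chosen deliberately, for comparison with the WHO-led study, and that one wording at all three assessments keeps the scale constant. The reason is sound for T0 and T2. It does not explain why a six-month look-back suits an 8-week assessment.

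The second defence concerns size, and it stands. The item asks for a typical week, not a time-weighted mean, and people may answer from recent weeks. The 31% is a share of calendar time, not a measured dilution.

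Four stronger readings are tempting, and the documents do not support them:

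- **T1 cannot show a treatment effect.** About 31% of the window is on treatment, and randomised arms have the same expected drinking beforehand. The earlier weeks dilute the contrast. They neither remove it nor favour an arm.
- **The primary outcome is diluted too.** The article does not state the recall frame of the AUDIT as fielded, so nothing here shows this.
- **T2 is compromised as well.** For these items the T2 window matches the time since randomisation, so the between-arm contrast is valid. It does include the 8 treatment weeks, so it is not a purely post-treatment measure.
- **The purpose of the three dates fails altogether.** Drinking motives, motivation for change and mental health are also measured at all three assessments, and no six-month window is stated for them.

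**Conclusion.** The point holds for two secondary outcomes at one non-primary time point. The wording and the schedule are explicit, and the 69% follows from them directly (about 62–69% across the ways of counting shown). Attenuation of the T1 contrast is probable. Its size is not known: 0.07 SD and the power of about 14% depend on averaging over the window and on a borrowed effect size, and the visible share could be anywhere from near 0% to 100%. That uncertainty is itself part of the problem, because nobody could say which period a T1 answer describes.

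The conflict with the Study design section is confined to these two items: for them, the T1–T2 comparison cannot be cleanly read as intervention effect against follow-up effect. The change is worth making, but it does not threaten the trial's main conclusion.

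**What to change.** - At T1, ask both items for a typical week over the past 8 weeks, that is, since baseline. This can replace the six-month wording or be added beside it.
- Keep the six-month wording at T0 and T2, which preserves the comparison with the WHO-led study.
- Flag participants who answered T1 under the old wording, since recruitment began in March 2019 and some may already have passed T1.
- If the wording can no longer be changed, state before analysis that T1 on these two items is not interpreted as the end-of-treatment effect, and that the T1–T2 change is not interpreted as a follow-up effect.

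The cost is two web items at one assessment. The downsides are small: the new T1 window differs from the T0 window, and T1 data exist in two versions. Adding the new items beside the old ones keeps one series comparable throughout, for two extra questions. The fallback costs only a sentence, but leaves consumption during treatment without a clear between-arm measure.
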